### Nurses

All nurses who are part of a nursing home ward are eligible to participate. Those who are not involved in care delivery in all ADL are excluded. Before the start of the study, all nurses allocated to either the intervention or control condition will receive a non-committal information letter by email explaining study details and a link to the digitalized questionnaire of the study. After consideration, nurses will be asked whether to provide online informed consent to participate. After signing the digital informed consent form, participants are directed to the baseline questionnaire.

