### Procedure and recruitment of participants

To examine the program’s effectiveness and cost-effectiveness, two participant groups will be recruited, i.e., nurses working in nursing home care and geriatric clients receiving nursing home care. Care organizations across the Netherlands are able to take part in the study as the SELF-program is widely disseminated through various (social) media platforms and national conferences. To be eligible to participate, organizations have to offer nursing home care. In case of organizational willingness to participate, formal approval of the board of directors will be requested and the client council will be informed about the study. In close agreement with organizational boards and team and location managers, nursing home wards will be selected to participate in the trial. Wards hosting somatic clients, as well as wards where psychogeriatric clients reside are eligible to be included in the study. Within an organization, dyads will be created consisting of two nursing home wards, which will then be pair-matched according to size and ward type, e.g., somatic or psychogeriatric ward. Of the two included wards from a dyad, one will be randomly allocated into the intervention group (SELF-program) or into the control group (care as usual), and clients residing at a ward will be allocated accordingly. Randomization will be conducted by means of computer-randomization using *random.org.* The unit of intervention will be the care ward, the unit of analysis will be the nursing care professional or the resident respectively.

To minimize the probability of contamination bias, dyads will be created of wards that do not collaborate in daily practice. In case of collaboration between wards, something likely to occur within nursing homes, randomization will take place on location level. Nursing home organizations in the Netherlands usually consist of multiple locations, which in turn consist of a varying number of wards. In the event of collaboration between wards within a location, the entire location is included in a dyad with a pair-matched comparator location. For example, a nursing home location with three collaborating psychogeriatric wards, will be pair-matched with a similar location.

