**ENROLMENT:**					
**Eligibility screen**	X				
**Informed consent**	X				
**Allocation**		X			

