**ASSESSMENTS:**					
**Nurses:**					
*** Demographic variables***		X			
*** MAINtAIN questionnaire***		X		X	X

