**Mechanisms of impact**			
Mechanisms assumed to produce change in outcome behavior	Interventionists	Questionnaire (31 items) Focus groupinterviews	Baseline, 3 months and 9 months after baseline

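### The text invites, consents and baselines nurses after their ward is allocated, Table 2 puts consent before allocation, and neither secures a baseline taken before the arm can be known

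*Protocol article*

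**What the plan says.** Under Procedure and recruitment of participants, the randomised unit is the ward, or the location where wards collaborate, within a matched dyad: "Of the two included wards from a dyad, one will be randomly allocated into the intervention group (SELF-program) or into the control group".

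The Nurses subsection then gives the recruitment order. The letter with the questionnaire link goes out as follows: "Before the start of the study, all nurses allocated to either the intervention or control condition will receive a non-committal information letter by email". Next: "After consideration, nurses will be asked whether to provide online informed consent to participate". Then: "After signing the digital informed consent form, participants are directed to the baseline questionnaire".

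Table 2 gives a different order. The row "Informed consent" is marked in the enrolment column (-t1), as is the eligibility screen. Allocation is marked one column later (0). In the nurses' block, the row "MAINtAIN questionnaire" and the demographics have their baseline mark in the allocation column. The client baseline measures are also marked there.

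The primary outcome is the eight-item ADL part of the MAINtAIN, which nurses complete about themselves. Data analyses, Effect evaluation, takes the treatment by time interaction from a three-level mixed model as the effect and reads it as Cohen's d. The sample size section targets d = 0.4.

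**The concern.** In a cluster trial, randomising wards balances the nurses who work there. It does not balance the nurses who choose to take part once the ward's arm is settled. If consent comes after allocation and the arm is known, willingness to be trained can affect enrolment differently in the two arms. The article's Theoretical background treats motivation and intention as drivers of behaviour change, so willing nurses may also change more.

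The baseline answers are exposed in the same way. A nurse who knows that training is coming may rate her current behaviour more critically, or more favourably, than one who expects nothing to change. As the effect is a difference in change from T0, the T0 answers are part of the estimate.

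Client outcomes share the second exposure, because the primary responsible caregiver completes those questionnaires, alone or with the client.

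**Working it through.** **Order of events, side by side**

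| Step | Nurses subsection | Table 2 |
|---|---|---|
| Eligibility screen | no time point given | before allocation (-t1) |
| Invitation letter | after allocation | not shown |
| Informed consent | after allocation | before allocation (-t1) |
| Nurse baseline | after consent, so after allocation | in the allocation column (0) |

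The conflict concerns enrolment, and consent above all. On baseline the two sources do not conflict, but neither places it before allocation. Saying that the letter precedes the start of the study does not settle the matter, since its recipients are already described as allocated.

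**Could nurses know their arm at T0?** The article does not say so. Some features make it plausible. The training runs for three months, and T1, directly after it, falls about three months after baseline, which leaves little time between baseline and the kick-off. Each SELF team must also supply an assistant-trainer.

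**Effect on the estimate.** The plan gives no figure for this risk, so there is none to reproduce. Let b0 be the arm-related shift in mean answers (SELF minus control) at T0 and bF the same shift at follow-up, in SD units. With complete data:

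estimated interaction = true interaction - b0 + bF

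- If bF = b0, the shift cancels.
- If bF = 0, the bias is -b0, the whole of the shift.

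Take the target of 0.40 as the true effect and assume shifts confined to T0. The values of b0 are assumptions, not figures from the article.

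| Assumed size of b0 (SD) | Share of 0.40 | Estimate if SELF baseline is raised | Estimate if it is lowered |
|---|---|---|---|
| 0.05 | 12.5% | 0.35 | 0.45 |
| 0.10 | 25% | 0.30 | 0.50 |
| 0.20 | 50% | 0.20 | 0.60 |

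**Power for the raised case.** Inputs from the sample size section are 165 nurses per arm, 15 per ward and an ICC of 0.05. The design effect is 1 + 14 x 0.05 = 1.7, and 165 / 1.7 = 97.1 effective nurses per arm, ignoring attrition. Power is approximately Phi(d x sqrt(97.1/2) - 1.96):

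- d = 0.40: 0.80
- d = 0.35: 0.68
- d = 0.30: 0.55
- d = 0.20: 0.29

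**Selective consent.** A difference in level between enrolled nurses that is the same at T0 and follow-up has bF = b0 and drops out. Selection biases the interaction only through a difference in expected change. The article gives nothing from which to size that.

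**The case against.** **Table 2 may describe enrolment of organisations or wards, since its enrolment rows name no level.** This reading is open but weak: the article speaks of board approval for organisations and uses informed consent only for nurses and clients. If it were accepted, the text alone would govern, and it puts nurse consent after allocation.

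**The letter may not reveal the arm, and the full protocol may describe concealment.** This stands as a limit. The article supports saying that knowledge of the arm can influence enrolment and answers, not that it will. The point rests on the order that the article states and on the contradiction within it.

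**All eligible ward nurses are invited, so no recruiter selects them.** This is true, and it removes one route to bias. Voluntary consent leaves self-selection open, and neither intention-to-treat analysis nor adjustment for measured covariates removes its effect.

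**Stronger readings that the article does not support:**

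- A reader might infer that baseline after allocation contradicts Table 2. It does not, because the table marks baseline in the allocation column. Following the table as printed would not secure a baseline before allocation.
- A reader might take the Table 3 entry for interventionists, timed "Baseline, 3 months and 9 months after baseline", as proof that the arm is known at baseline. It names a data source. The items could be asked of everyone and analysed later for those who received the programme, and knowledge held by the researchers is not knowledge held by nurses.
- A reader might turn unequal consent directly into bias. Assume consent of 60% v 80% and a correlation of 0.3 between willingness and outcome: 0.3 x (0.644 - 0.350) = 0.088 SD. That is a difference in level, which cancels from the interaction if it persists.
- A reader might infer that clients also consent after allocation. The Geriatric clients subsection says only that consent precedes data collection and that eligibility depends on residence when the ward is included.

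**Conclusion.** The point holds. The text and Table 2 disagree on whether nurses consent before or after allocation, and neither secures a baseline before allocation. With an open ward-level programme and a self-reported primary outcome, following the text as written leaves both enrolment and T0 answers open to influence by the arm.

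The size cannot be derived from the article. For an arm-related shift confined to T0, the assumed range of 0.05 to 0.20 SD gives a bias of 12.5% to 50% of the target d = 0.4, in either direction. A persisting shift would largely cancel. Selective enrolment biases the effect only if willingness predicts change, which is consistent with the programme's theory but not quantified.

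**What to change.** 1. For each dyad not yet drawn, complete nurse consent and the nurse T0 questionnaires in both wards before the random.org allocation is made, or at least before it is disclosed to the wards. Do the same for the client T0 questionnaires, since caregivers on the same wards complete them.
2. Amend the Nurses subsection so that the letter goes to nurses of wards awaiting allocation.
3. In Table 2, keep eligibility and consent where they are and move the baseline marks for nurses and clients to before allocation.
4. For dyads already drawn, report by arm how many nurses were invited, consented and completed baseline. Recruitment began in spring 2021 and was expected to run to spring 2022, so there may be several. Treat any analysis that excludes them as a sensitivity analysis only, because the sample size section plans just 11 dyads and exclusion could remove much of the trial.

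The cost is that the draw, or its disclosure, and the scheduling of trainers move somewhat later in each dyad. No extra measurements are needed.

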### Geriatric clients

Geriatric clients are eligible to participate if they are residing at the concerned ward at time of ward inclusion. Clients are excluded from participation when aged < 65 years old, or when terminally ill or bedbound. In addition, those with a temporary stay (< 6 months) are excluded. Data collection for geriatric clients will be accomplished by the primary responsible caregiver, who will be asked to fill in the questionnaires for their client(s). Depending on the level of cognitive and physical impairment, the primary responsible caregiver can fill in the questionnaire alone or together with the geriatric client. Before data-collection of geriatric clients, written informed consent will be obtained from either the client itself or a responsible party, generally a family member appointed as the primary contact person of the client.

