### Nurses

Since the SELF-program is directly pointed at nurses, this participant group is considered the primary target group. The primary outcome for nurses, i.e. the level of stimulation behavior of self-reliance in ADL among geriatric clients, will be assessed at baseline (before implementation of the SELF-program; T0), directly after implementation of the SELF-program (approximately 3 months after the baseline assessment; T1), and 9 months after the baseline assessment (T2). The validated self-report MAINtAIN questionnaire will be used to assess the primary outcome measure [42]. The MAINtAIN comprises three subscales with a total of 19 items, representing whether nurses stimulate clients in a variety of daily activities, that can be rated on a 9-point Likert scale, ranging from ‘never’ to ‘always’. Of the 19 items, 8 deal with encouraging ADL, 6 with encouraging instrumental ADL and 5 with encouraging general function and physical activity. The 8 items focusing on encouraging ADL will be used as a the primary outcome.

Demographic characteristics of nursing care professionals will be assessed at baseline only. These include the participants’ gender (male, female or open answer option), age, education level (low; no education up to lower technical education, medium; general secondary education up to secondary vocational education or high; school of higher general secondary education up till university degree), nursing profession (nursing aide, certified nursing assistant or registered nurse), years of working experience in nursing care and within the current care setting, and number of working hours according to contract.

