### Geriatric clients

The main outcome for geriatric clients, i.e. self-reliance in daily functioning, will be assessed at baseline (before the implementation of the SELF-program for care professionals; T0), directly after implementation of the SELF-program (approximately 3 months after the baseline assessment; T1), and 6 months after the baseline (T2). The relative shorter follow-up period at T2 for geriatric clients compared to the one for nursing care professions will be applied because a higher level of turnover of geriatric clients is to be expected given the nature of the setting. The Groningen Activity Restriction Scale (GARS-4) will be used to assess the perceived self-reliance in daily functioning of geriatric clients [43]. The GARS-4 consists of two subscales with a total of 18 items that can be rated through a hierarchical 4-point answering scale ranging from ‘Yes, I can do the particular task completely independently without any effort’ to ‘No, I cannot do the particular task completely independently, only with help from others’. Of the 18 items, 11 items examine self-reliance in ADL activities and 7 items examine self-reliance in instrumental ADL activities. Only the 11 items of the ADL-subscale will be assessed given the 7 items of the instrumental ADL-subscale are less applicable to geriatric clients residing in nursing homes.

Demographics of geriatric clients will be assessed at baseline only. These include the client’ gender (male, female or open answer option), age, education level (low; no education up to lower technical education, medium; general secondary education up to secondary vocational education or high; school of higher general secondary education up till university degree), living arrangement (single, married, in a relation whether or not living together, divorced, widowed), years of receiving nursing home care, and whether and from whom the client received informal care. For both their own and their client questionnaires, nurses will be prompted periodically to complete either the baseline or follow-up questionnaires in case these are yet to be completed.

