This study set up has several strengths. First, the SELF-program has been developed within the cyclic framework of the Medical Research Council, which addresses the systematic development, feasibility testing, evaluation and implementation of complex interventions [50]. After the development of the SELF-program, taking into account lessons learned and implications gathered from process evaluations of previous Dutch FFC-based interventions, the SELF-program was feasibility tested in one nursing home ward. The SELF-program was considered feasible in practice and valuable adaptations have been applied prior to the onset of the intended CRT in nursing home care. Another strength, and with that building on implications from previous work, is the incorporation of a more integrated theory of behavior change. More specifically, the SELF-program incorporates a thorough sequential dual behavior change process in which first attempts are made to change the behavior of nurses before they are enabled to improve client’s activity behavior. Although the FFC-philosophy includes behavior change determinants as mechanisms to alter care professionals behavior, recent work questions whether addressing these determinants is sufficient to bring about change. Consequently, it is advocated to include a broader spectrum of behavior change determinants by using integrative behavior change models such as the one addressed in the SELF-program [32]. In addition, we adhere to the suggestions addressed by Lee and colleagues and Verstraten and colleagues to conduct thorough evaluations of FFC-based programs and to use research methods aimed at producing more rigorous burdens of proof [25, 54]. Limitations of the study include the subjective approach of data-collection, i.e., using self-report questionnaires. However, objective measures such as researcher-based observations or videos taken from daily practice may interfere with the client’s and care professionals privacy, for example when examining stimulation behavior and self-reliance in care activities related to personal cleanliness. In line, although it is common in healthcare to collect data from clients with psychogeriatric complaints by their first responsible caregiver – given they have direct and frequent contact to the client in question – we have opted to collect data from all nursing home clients by their primary responsible caregiver. This implies that data from clients with somatic backgrounds will also be collected by their first caregiver, although they might be self-capable to provide the data. However, to address the uniformity of data-collection, and given somatic and psychogeriatric complaints commonly co-occur in Dutch institutionalized care, this approach was considered most feasible. Last, the follow-up period chosen in the CRT is based on practical and financial considerations. However, regarding the outcomes assessment in geriatric clients, i.e., self-reliance in daily activities, it is debatable whether a follow-up period of 6 months is long enough to detect changes. Since the SELF-program assumes that primarily a behavior change is required in care professionals, its translation into adequate changes in day-to-day care practice and subsequently client’s self-reliance may – if any – occur beyond this time period.

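### Client outcomes are completed by the ward nurse, alone or with the client, and no stated rule holds that mode or the rater constant across waves, although nurses are trained in one arm only

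*Protocol article*

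**What the plan says.** All of this is in the protocol article.

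- **Who answers, and how.** Under Geriatric clients (recruitment), the primary responsible caregiver completes the client forms, and subject to the client's cognitive and physical impairment "the primary responsible caregiver can fill in the questionnaire alone or together with the geriatric client". No threshold of impairment is given, and the sentence does not mention measurement waves.
- **That caregiver is a ward nurse.** Under Geriatric clients (data collection): "For both their own and their client questionnaires, nurses will be prompted periodically to complete either the baseline or follow-up questionnaires". The Economic evaluation section takes its client data from the same caregiver.
- **That nurse is the target of the programme.** Under Nurses (data collection): "Since the SELF-program is directly pointed at nurses, this participant group is considered the primary target group". Clients are allocated with their ward (Procedure and recruitment of participants), so rater and client share an arm. The training runs over three months and T1 follows directly after it.
- **The justification.** The Discussion says "we have opted to collect data from all nursing home clients by their primary responsible caregiver", including somatic clients who might be able to answer for themselves, and explains: "However, to address the uniformity of data-collection, and given somatic and psychogeriatric complaints commonly co-occur in Dutch institutionalized care, this approach was considered most feasible". It lists subjective, self-report questionnaires and caregiver completion as limitations.
- **The analysis.** Under Data analyses, the effect model has treatment, time, their interaction and background characteristics, with random effects for ward and subject. The principal economic analysis is cost per QALY, based on EQ-5D-5L.

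**The concern.** How far the client takes part in answering is left to vary, and the person applying that latitude is the person the programme tries to change. The programme teaches nurses to look at what clients can do and to motivate and enable them. A nurse who has absorbed this may sit down with the client at T1 for a form that she completed alone at T0. An untrained nurse in the control arm has no such prompt.

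GARS-4 is described as measuring perceived self-reliance, with answer options worded in the first person, so it is plausible that the answer depends on who gives it. If joint and caregiver-only answers differ on average, and switching differs between arms, part of the measured change is a change of method. Neither randomisation, the ward and subject random effects nor baseline adjustment removes a shift that arises after baseline in one arm.

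At stake are the main client outcome (GARS-4, also the outcome of the cost-effectiveness analysis) and the QALYs. The nurses' own MAINtAIN score, the trial's primary outcome, is not affected by this mechanism.

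**Working it through.** **1. Is there a figure in the plan to reproduce?** No. The article gives no share of clients answered for jointly, no difference between modes and no rate of rater change. What follows illustrates scale only.

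**2. The passages side by side.** The recruitment section fixes the supplier of the data (the caregiver) and leaves the client's involvement open (alone or together). The Discussion's appeal to uniformity, "However, to address the uniformity of data-collection", supports having one type of supplier for all clients. It does not cover how far the client is involved, or whether that stays constant from wave to wave. The limitations do not mention that the rater is trained in one arm only.

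**3. Where the shift would land.** The effect model has no term for mode or rater. An arm difference in mode change between T0 and T1 or T2 has the same form as a treatment-by-time effect, and that coefficient would absorb it.

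**4. Size of the bias.** Bias in SD units = (arm difference in the share of clients who change mode) × (mean difference between modes in SD). Both inputs are assumptions.

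**5. Against the precision of the trial.** From Sample size calculation: 165 per arm, 11 wards of 15 per arm, ICC 0.05. Using that ICC for client outcomes is a further assumption, because it was set for the nurse outcome.

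- Design effect = 1 + (15 − 1) × 0.05 = 1.70.
- SE of the standardised difference = √(2 × 1.70 / 165) = 0.144.
- Two-sided type I error with bias b = Φ(b/SE − 1.96) + Φ(−b/SE − 1.96).

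| Arm difference in switching | Mode difference | Bias (SD) | Type I error |
|---|---|---|---|
| 10 points | 0.3 SD | 0.03 | 0.055 |
| 10 points | 0.5 SD | 0.05 | 0.064 |
| 20 points | 0.3 SD | 0.06 | 0.070 |
| 20 points | 0.5 SD | 0.10 | 0.107 |
| 30 points | 0.3 SD | 0.09 | 0.096 |
| 30 points | 0.5 SD | 0.15 | 0.181 |

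With 12 clients per ward instead of 15, the SE is √(2 × 1.55 / 132) = 0.153, and the 20-point rows become 0.068 and 0.100, so the picture is the same.

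**6. For comparison, a direct rating shift.** If trained nurses simply scored clients 0.2 SD differently, with no change of mode (again an assumption), the type I error would be 0.29. This is potentially the larger problem, and holding the mode fixed leaves it in place.

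**7. QALYs.** The documents give no SD for utilities, so the bias cannot be converted to QALYs. The mechanism is the same because the same nurse completes EQ-5D-5L.

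**The case against.** The strongest reply has four parts.

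*The text does not say that the nurse chooses afresh at each wave.* Correct. A reader might infer a free choice per wave, but the recruitment section names a criterion, impairment, and is silent on waves. What stands is that the criterion has no threshold and that no rule of constancy is stated. Nor does the choice concern trial participation, which is settled by consent from the client or a responsible party.

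*The Discussion and the recruitment section do not contradict each other.* Largely correct. A reader might see a flat contradiction, but uniformity can be read as the caregiver supplying the data for everyone, which both sections say. What stands is narrower: the argument from uniformity does not reach the client's involvement, so it cannot reassure on that point.

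*Recording of mode and rater may be in a fuller document, and proxy report is already disclosed.* The article's silence on recording is not held against it. But the article does state a variable mode, and its disclosure stops short of the arm-linked mechanism.

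*The arm link is inference and the numbers are assumed.* Both are true. The training content described concerns stimulating daily activities, not questionnaires, and no direction can be established. A reader might also scale the bias against the planned effect of 0.4, or apply the 20% attrition to count clients with a new rater. The documents support neither: both figures belong to the nurse outcome, no client effect size is planned, and attrition does not tell how many clients are re-rated by someone else.

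**Conclusion.** The point holds as a weakness in how the client outcomes are measured. The person completing GARS-4 and EQ-5D-5L belongs to the group that the programme trains, in one arm only. That person may answer with or without the client, and the article states no rule that holds mode or rater constant from T0 to T2. A differential shift could mimic or hide an effect.

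On mode alone the likely size is modest: 0.06-0.10 SD, with type I error of about 0.07 to 0.11, under a 20-point arm difference in switching, a 0.3-0.5 SD mode difference and an ICC of 0.05 for clients. None of these is a documented value for client outcomes. The documents do not show that such a shift will occur. They show that the stated procedure does not guard against it.

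The change is worth making because it is cheap and because mode and rater, if not recorded at the time, cannot be reliably recovered afterwards.

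**What to change.** 1. Set the respondent mode (caregiver alone, or jointly with the client) for each client at T0, before training starts. Keep it at T1 and T2, with the same rater where possible.
2. Record the mode used and a pseudonymous rater code on each client questionnaire at each wave.
3. Report changes of mode and rater by arm. Add a supportive sensitivity analysis that uses the T0 mode, by adjustment or stratification. Treat any analysis limited to clients with unchanged mode and rater as exploratory, because it conditions on behaviour after randomisation that the programme may itself affect.
4. Align the Discussion with the recruitment section: say that uniformity refers to who supplies the data, and that the client's involvement varies.
5. State as a limitation that client outcomes are rated by unblinded nurses trained in one arm only. Steps 1 to 3 do not remove this.

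Cost: two fields in questionnaires that are already digital, one instruction to caregivers, one table and one sensitivity analysis. The article says that amendments go back to the ethics committee. The downside is less flexibility when a client's cognition declines; a switch is then allowed and recorded.
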